**Intervention**

All participants will receive instantaneous feedback from the health screen in-line with standard NHS recommendations for healthy living. Participants who drink within recommended limits, do not smoke, eat five or more portions of fruit and vegetables a day or undertake 150 minutes or more of moderate or vigorous physical activity a week will be congratulated for leading a healthy lifestyle and reducing their risk of heart disease or cancer, for example. Participants who drink above recommended limits, smoke, eat less than 5 portions of fruit and vegetables a day or do less than 150 minutes of moderate or vigorous physical activity a week will receive feedback on the governments recommendations and the benefits of changing their behaviour (to reduce their risk of harm). This brief advice will be accompanied by hyperlinks to corresponding pages of the NHS Choices and NHS Livewell websites for further information. Participants drinking above recommended limits will receive brief advice on the harms of excess drinking, along with a hyperlink to the Down Your Drink website. The Down Your Drink website is for people wanting to determine how much they are drinking, whether it is a problem for them and for support with making changes. Down Your Drink is an extensive online brief intervention and may or may not be used or needed by all employees. This will be explored in the follow-up questions.

*The Down Your Drink website*

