*Engagement with online alcohol intervention (Down Your Drink)*

The number of employees from each organisation who access Down Your Drink, i.e. who register with the website, will be reported. The characteristics (i.e. demographics – collected at baseline) of those participants who register with Down Your Drink will be compared descriptively with those participants who did not register. Of those participants that do register with Down Your Drink, the number of logins and number of pages visited per login will be reported; these data will be collected by Google Analytics.

The follow-up questionnaire will include questions about the Down Your Drink website. Firstly, participants will be asked if they accessed the Down Your Drink website. If they did access Down Your Drink, they will be asked what they like about the website, what they dislike and how it could be improved. There will be a list of tick box options to choose from and a free text box for their own comments. Participants who did not access the website will be asked to provide their reasons. Once again they will be presented with a list of tick box options and a free text box for comments. Participants will also be asked if they have accessed any other alcohol-related resources during the three month study period, and if so, to detail what these resources were.

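### The Down Your Drink engagement comparison sets registrants against all non-registrants, most of whom may never have been shown the link

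*Protocol*

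**What the plan says.** The Intervention section of the protocol gives health feedback to everyone. Participants drinking above recommended limits receive, in addition, brief advice on harms, "along with a hyperlink to the Down Your Drink website". Nothing in the section offers that link to anyone else. Under Baseline data collection, an AUDIT-C score of 5 or more marks drinking above recommended limits.

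Under Outcomes and outcome measures, in the part on engagement with Down Your Drink, three things are fixed:

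- The count: for each organisation, the number of employees "who access Down Your Drink, i.e. who register with the website". No denominator is given.
- The comparison: the demographics of those "who register with Down Your Drink will be compared descriptively with those participants who did not register". The group is not limited to people shown the link.
- The questionnaire: "Firstly, participants will be asked if they accessed the Down Your Drink website". Those who say yes are asked for their opinions of the site. For the rest, "Participants who did not access the website will be asked to provide their reasons".

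Follow-up data collection states that every participant gets the same questions. Engagement and suitability form Objective 4, and the Analysis section says the level of engagement will inform the definitive trial.

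**The concern.** A comparison of users with non-users is informative about engagement only if both groups had the chance to use the site. Here the non-registrants contain two different kinds of people: drinkers above the limits who were shown the link and did not register, and participants below the threshold who were not shown it. Any characteristic associated with drinking above limits will then separate registrants from non-registrants even if it has nothing to do with engagement. It can also hide a real difference in uptake.

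The same mixing affects the reasons for non-access, since people never shown the link are asked why they did not follow it. A bare count per organisation has a related weakness: it moves with the number of risky drinkers recruited as well as with their willingness to use the site. Someone planning the definitive trial could then target the wrong groups or misjudge demand.

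**Working it through.** The protocol states no engagement figure, so there is nothing to reproduce. The check has three parts.

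**1. How much of the comparison group was never offered the site?**
Input: 39% scored AUDIT-C 5 or more in the earlier single-company trial described in the Background. Assumption: the same share applies here. Then 100% − 39% = 61% of participants are not shown the link. With uptake u among those shown it, the share of non-registrants never shown it is 0.61 / (1 − 0.39u):

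- u = 10%: 0.61 / 0.961 = 63%
- u = 30%: 0.61 / 0.883 = 69%
- u = 50%: 0.61 / 0.805 = 76%

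**2. What does this do to the comparison?**
Inputs: 26% of men and 17% of women drinking above weekly limits (Background, England 2010). Assumptions: equal numbers of men and women, these rates stand in for being shown the link, and uptake u is the same in both sexes.

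Male share of registrants = 0.26u / (0.26u + 0.17u) = 26/43 = 60.5%, whatever u is.
Male share of non-registrants as planned = (1 − 0.26u) / (2 − 0.43u).
Male share of non-registrants shown the link = 0.26(1 − u) / [0.43(1 − u)] = 60.5%.

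| Uptake u | Registrants, % male | All non-registrants, % male | Gap as planned (points) | Gap among those shown the link |
|---|---|---|---|---|
| 10% | 60.5 | 0.974/1.957 = 49.8 | 10.7 | 0 |
| 30% | 60.5 | 0.922/1.871 = 49.3 | 11.2 | 0 |
| 50% | 60.5 | 0.870/1.785 = 48.7 | 11.7 | 0 |

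The planned table shows men as the more engaged sex when uptake is identical. The error can also run the other way. Suppose uptake is 20% in men and 30% in women. Registrants are 0.052 / (0.052 + 0.051) = 50.5% male and all non-registrants 0.948 / (0.948 + 0.949) = 50.0% male, so no difference appears. Among those shown the link, non-registrants are 0.208 / (0.208 + 0.119) = 63.6% male, and the difference is visible.

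**3. What does the missing denominator do?**
Take two organisations with the same 30% uptake among those shown the link, one with 22% of participants above limits (the Background's figure for adults in England) and one with 39%. Per 100 participants they yield 0.22 × 30 = 6.6 and 0.39 × 30 = 11.7 registrants. Engagement looks nearly twice as high in the second, and none of that difference is engagement.

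**The case against.** The strongest reply is that this is an analysis detail. AUDIT-C is recorded for every participant, so the table can be restricted later, and the statistical analysis plan, which the protocol cites and which is not available here, may already do so. It stands that no data would be lost. But the protocol does not leave the comparison group open: it names it as the participants who did not register. Giving the same questions to everyone is likewise a statement of the protocol.

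A second reply is that little depends on it. The analysis is largely descriptive, feasibility is judged on eligibility, recruitment and retention together with the acceptability responses, and engagement has a supporting role. That stands and limits the weight of the point.

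A reader might also infer something stronger: that equating access with registration undercounts engagement, contradicts the questionnaire, and loses the reasons of people who looked but did not register. The documents do not support that much. The questionnaire item is summarised, not shown, and may define access. Nothing says how much of the site can be seen before registering. Visitors who report access can still say what they disliked. Registration is a legitimate threshold, and a system record need not match a self-report that exists only for follow-up responders. What remains is one word used for the web measure and again for the questionnaire without being tied together.

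**Conclusion.** The point holds for the comparison group, the denominator and the reasons for non-access. As written, the comparison mixes declining the site with never being offered it, and the per-organisation count mixes engagement with the prevalence of risky drinking. In the illustration the spurious sex gap is 11 to 12 points for uptake between 10% and 50%, and about 63% to 76% of the comparison group was never shown the link.

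These sizes are not predictions. They rest on the 39% from a different workforce, on national survey rates that use weekly limits rather than AUDIT-C, on equal sex numbers and on assumed uptake. The direction of the problem needs only that the link goes to drinkers above the limits, and that the characteristic compared is related to drinking.

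That engagement is materially undercounted is not established: the size of any group that visited without registering cannot be estimated from the document. The point merits correction because it alters a stated result for a stated objective, but no stated sample size rests on it and feasibility is not judged on it.

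**What to change.** - Restrict the registered versus not registered comparison to participants shown the link (AUDIT-C 5 or more). List any registrants below the threshold separately.
- For each organisation, report the number shown the link and registration as a number and a percentage of that group.
- Ask for reasons for non-access only of participants shown the link. If the questionnaire is already fixed, tabulate the reasons for that group only.
- Label the web measure *registered* instead of *accessed*. If the questionnaire can still be changed, ask *visited* and *registered* as two items.

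The first two changes, and the tabulation in the third, use AUDIT-C and registration data already planned for collection and cost a few lines of text. The two-item question adds one tick box. Logging clicks on the link would separate visiting from registering objectively, but it is optional: the document does not show whether the study website can still be altered.

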**Participants**

Eligible participants are employees at each of the six workplaces, providing informed consent. As employees of these companies, participants will be adults with the ability to read English. Employees will need to gain access to the Internet to participate in this study.

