**Baseline data collection**

*Health screen*

Participants will be asked to answer questions of a range of behaviours known to impact on their health and wellbeing, namely alcohol, smoking, diet and physical activity. The 3-item AUDIT-C questionnaire will be used as an initial screen for alcohol misuse ([37](#_ENREF_37)), with a score of five or more indicating consumption above recommended limits ([36](#_ENREF_36)). The AUDIT-C comprises the first 3 consumption questions from the WHO Alcohol Use Disorders Identification Test (AUDIT) ([38](#_ENREF_38)). Questions relate to the frequency of alcohol consumption, quantity of alcohol consumed on a typical drinking day, and frequency of drinking more than 6 (women) or 8 (men) drinks on one occasion. For participants scoring 5 or more on the AUDIT-C, the remaining seven questions of the AUDIT will then be presented which focus on alcohol-related harm. Questions on smoking status, consumption of fruit and vegetables and level of physical activity will also be included in the health screen, using the same approach as the HOW study ([36](#_ENREF_36)).

*Demographics*

Participants will be asked to provide demographic information, consisting of gender, year of birth, ethnicity, occupational classification (categories to be supplied by the occupational health lead from each organisation). Participants will also be asked to provide an email address that will allow them to be contacted again in three months’ time. Demographic data will be collected at the end of the health screen, before provision of feedback on health behaviours.

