**Follow-up data collection**

All participants will be contacted by email three months after baseline data collection to complete follow-up questionnaires online. The emails will contain a hyperlink to the online battery of questionnaires. All participants will receive the same questions at follow-up. Details of the type of data collected at follow-up are provided below under *Outcomes and outcome measures*.

The study will be registered with the UCL data protection officer. The data will be collected and stored in accordance with the Data Protection Act 1998 and will be disposed of in a secure manner. Participants will automatically be assigned a unique identifying number when consenting to take part in the study. All outcome data will be anonymised and identifiable only by the unique ID number. Data will be automatically loaded into a secure, password protected, on-line database, which can only be accessed by the research team. The following measures will be taken to ensure data security:

•The webserver will be protected by a firewall

•Personal data will be encrypted and entered via data entry pages hosted on a Secure Server (https://)

•Email addresses, personal data and research data will be stored in separate, distinct database tables

•Access to database tables will be strictly limited to those actively involved in the project, who will be issued with a username and password

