**Analysis**

This feasibility study will aim to recruit (i.e. an employee providing informed consent, completing the health screen and receiving personalised feedback) at least 30 participants from each site to provide reasonable estimates of study parameters ([39](#_ENREF_39)). The analysis will be largely descriptive. Baseline data will be presented as the numbers and percentages of participants who drink above recommended limits, smoke, eat less than 5 portions of fruit and vegetables a day or do less than 150 minutes of moderate or vigorous physical activity a week. These data will also be presented graphically in bar charts. Follow-up AUDIT data will be compared descriptively with baseline AUDIT data. Data from the follow-up questionnaires on the acceptability of the study will be presented as numbers and percentages answering each of the multiple choice questions. These data will also be presented graphically in bar charts to aid interpretation.

Rates of eligibility, recruitment and retention will help determine whether a definitive multicentre trial of eSBI is feasible in these workplace settings, with success criteria detailed in the statistical analysis plan. Responses to questions on the acceptability and potential risk to employees of eSBI in the context of a research study in the workplace will provide more detailed information on whether to proceed to a definitive RCT. The design of a definitive trial will also be informed by the level of engagement with an extensive online alcohol intervention.

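### The Down Your Drink comparison and the non-use question include participants who were never given the link, so drinking status is mixed with engagement

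*Protocol*

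**What the plan says.** Entry to the study does not depend on drinking. Under Participants: "Eligible participants are employees at each of the six workplaces, providing informed consent". The AUDIT-C is given to all at baseline, "with a score of five or more indicating consumption above recommended limits".

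The link is given to a subset. Under Intervention: "Participants drinking above recommended limits will receive brief advice on the harms of excess drinking, along with a hyperlink to the Down Your Drink website". Participants within limits are congratulated, and no Down Your Drink link is mentioned for them.

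The engagement part of Outcomes and outcome measures reports the number registering at each organisation. It then says that the baseline demographics of participants "who register with Down Your Drink will be compared descriptively with those participants who did not register". On the questionnaire it says: "Participants who did not access the website will be asked to provide their reasons". Follow-up data collection adds: "All participants will receive the same questions at follow-up".

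The result has a stated use. Engagement and suitability form objective 4, and under Analysis: "The design of a definitive trial will also be informed by the level of engagement with an extensive online alcohol intervention".

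**The concern.** The group that can be expected to register is narrower than the group it is compared with. A participant within limits is not sent to the site by the study, so not registering says nothing about willingness to use it. When such people are counted as non-registrants, the comparison answers two questions at once: who drinks above limits, and who takes up the site when it is offered. Only the second bears on engagement. Sex, age or occupational class may well be related to drinking, and each could then appear related to engagement when it is not.

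The reasons for non-use have the same problem. A reply that the site was not needed is evidence on suitability when it comes from someone above limits who saw the link. From someone within limits who never saw it, the same reply is expected. If the two are pooled, they cannot be told apart.

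At stake is the reading of objective 4 and what it contributes to the design of the definitive trial. No test, error rate or sample size is affected.

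**Working it through.** The protocol states no expected uptake and no figure for this comparison, so there is nothing of its own to reproduce. The arithmetic below shows how large the mixing could be.

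**Inputs**
- N = 6 sites × 30 = 180, the minimum target (Setting; Analysis).
- p, the share given the link. 39% scored AUDIT-C 5 or more in the earlier workplace study (Background). For a range, 22% and 75% are the two national figures in Background for drinking above limits. They were not measured by AUDIT-C and are used here as assumptions.
- u, the share of those given the link who register. The protocol gives no value; 5% to 50% is assumed.
- Nobody registers without being given the link (assumed).

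**Share of non-registrants never given the link**

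Given the link = Np. Registrants = Npu. Non-registrants = N(1 − pu). Never given the link = N(1 − p). The share is therefore (1 − p)/(1 − pu), which does not depend on N.

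At p = 39%, Np = 70.2 and N(1 − p) = 109.8:
- u = 5%: 109.8/176.5 = 62%
- u = 10%: 109.8/173.0 = 63%
- u = 30%: 109.8/158.9 = 69%
- u = 50%: 109.8/144.9 = 76%

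At the ends of the prevalence range:
- p = 22%: 140.4/178.0 = 79% at u = 5%, and 140.4/160.2 = 88% at u = 50%
- p = 75%: 45.0/173.2 = 26% at u = 5%, and 45.0/112.5 = 40% at u = 50%

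**How drinking status could look like engagement**

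Assume a half-male workforce, 26% of men and 17% of women above limits (the Background survey figures, used as a stand-in for AUDIT-C 5 or more), and the same uptake u in both sexes among those offered.
- Men among registrants: 0.26/(0.26 + 0.17) = 60.5%, whatever u is.
- Men among all non-registrants: (0.5 − 0.5 × 0.26u)/(1 − 0.215u), where 0.215 = (0.26 + 0.17)/2. This is 49.8% at u = 10%, 49.3% at 30% and 48.7% at 50%.
- Men among non-registrants who were offered the link: 60.5%.

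The plan's comparison would show a gap of about 11 to 12 percentage points although men and women take up the site equally. Among those offered the link the gap is zero.

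**Effect of restricting the comparison** (p = 39%)

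Non-registrants fall from 173 to 63 at u = 10%, from 159 to 49 at 30%, and from 145 to 35 at 50%. The number of registrants does not change.

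**The case against.** The strongest reply is that this is one descriptive table in a largely descriptive feasibility study. The success criteria are tied to eligibility, recruitment and retention, and engagement only informs the later design. AUDIT-C is held for every participant, so the restriction can be applied at analysis, and the statistical analysis plan, which is not available here, may already do so. This lowers the severity but does not remove the point. The protocol names the comparator itself, and following it as written gives the mixed comparison. Descriptive results are also what this study is meant to deliver.

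A second reply concerns the reasons for non-use. Intervention acknowledges that not every employee may need the site and says follow-up will explore this. The tick-box list is not shown, and an option such as not needed or not offered could separate some replies. The statement that everyone gets the same questions cannot be fully literal either, since the questions branch on access. This stands as far as it goes: a reader might infer that the reasons table would be filled by people with no cause to use the site, but the unseen list does not allow that conclusion. It does nothing for the comparison of registrants with non-registrants.

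Three other inferences go too far. A reader might suppose that the protocol calculates uptake over all participants; it gives only a count per organisation, with no denominator. A reader might say that any demographic difference would reflect drinking alone; the unrestricted comparison mixes the two influences and does not remove engagement. And leaving baseline AUDIT score out of the compared characteristics is a choice, not an error.

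**Conclusion.** The point holds. The protocol offers the site to one group and compares registrants with a wider one, and it puts the non-use question to that wider group as well. Engagement is thereby mixed with drinking status.

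The size depends on assumptions. With prevalence as in the earlier workplace study, 62% to 76% of non-registrants would never have been given the link; over the wider assumed range it is 26% to 88%. It is tempting to say that most non-registrants were never offered the site. That follows at 39% but not at 75%, where the share is 26% to 40%, and the protocol does not fix the prevalence at these sites. Even the lowest value is enough to blur the comparison. The sex example shows how a gap could arise and does not predict one.

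Severity is moderate: the table is descriptive, it feeds objective 4 and the definitive trial's design, and it can be put right from data already collected.

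**What to change.** In the engagement part of Outcomes and outcome measures:
- State that registrants are compared with non-registrants among participants with baseline AUDIT-C of 5 or more who were shown the link.
- Tabulate reasons for non-use in that group, or separately by whether the link was shown.
- Report, for each organisation, the number registered alongside the number shown the link.
- Optionally, add baseline AUDIT score as a descriptor. The full AUDIT is already collected in this group, and Background asks whether the intervention suits the level of need.

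The cost is a change of wording, an analysis filter and smaller comparison groups. No new data are needed, and the follow-up questionnaire can stay as it is if the reasons are split at analysis.
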